#### Efficacy secondary outcomes (study population is given in brackets)

7.Normalized cumulative fluid balance measured in both groups at H24 and H72 after inclusion or death, whichever comes first, and at day 7 in alive patients. Fluid balance measured between inclusion and early time point (H24 or H72 or death) will be normalized by dividing it by the observation period duration and expressed in ml h^−1^. The fluid balance at H24 and H72 will be quantified using the same input and output items as per the primary outcome. The fluid balance at day 7 will be estimated based on the change in body weight between inclusion and day 7 [*ITT population*].8.Normalized cumulative UF_NET_ volume in both study groups at H24 and H72 after inclusion or death, whichever comes first. Cumulative UF_NET_ measured between inclusion and H24 or H72 or death will be normalized by dividing it by the observation period duration and expressed in ml h^−1^. The cumulative UF_NET_ volume will be computed based on the UF_NET_ volumes reported every 4 h between inclusion and 24 or 72 h after inclusion or death, whichever comes first [*ITT population*].9.PaO_2_ to FiO_2_ ratio and the extravascular lung water index measured with the cardiac output monitoring device, measured once a day from inclusion to H72 or death, whichever comes first. The FiO_2_ is the FiO_2_ set on the respirator or the high-flow nasal cannula device. In non-ventilated patients, the FiO_2_ will be estimated using the following formula: FiO_2_ = 0.21 + 0.03 × oxygen flow rate (in L min^−1^) [25] [*ITT population*].10.The number of ventilator-free days in both study groups, quantified as the number of days alive without mechanical ventilation, starting at the time of inclusion and censored at day 28 of inclusion. Mechanical ventilation weaning will be defined if invasive mechanical ventilation is not required for a continuous period of 48 hours or longer. A value of 0 is allocated if the patients died between inclusion and day 28. A value of 0 is also allocated if the patient is still receiving invasive mechanical ventilation at day 28 [24]. In case of multiple mechanical ventilation weaning episodes, only the last weaning attempt will be considered [*ITT population*].11.MAKE-90 assessed between inclusion and day 90 after inclusion in both groups. MAKE-90 comprises death before or at day 90, RRT dependence at day 90, and persistent stage 2 or 3 acute kidney injury (as per the KDIGO guidelines) at day 90. RRT dependence is present if the patient is still receiving CRRT at day 90 or if he has received an intermittent technique in the time frame of ±2 days around day 90. Persistent acute kidney injury is adjudicated based on a baseline plasma creatinine concentration (identified in the 6 months to 7 days before ICU admission), and the plasma creatinine measured at day 90 [6]. In case of missing baseline creatinine value, it will be retrospectively estimated [26]. Each element of the composite event will be evaluated separately [*ITT population*].12.Hospital and ICU length of stay, quantified as the duration, in days, between inclusion and hospital and ICU discharge (alive or deceased), respectively [*ITT population*].

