## Data collection and management

### Plans for assessment and collection of data {18a}

Investigators are responsible for the assessment and collection of outcomes, baseline, and other trial data. To improve the quality of data collected in regard to the hemodynamic protocol and its application every 4 h, a bedside case report form specific to the study arm will be made available, directly downloadable, and printable from the central web-based system Ennov Clinical® 7.5.720 after patient enrollment (Supplemental Materials 4 [intervention group] and 5 [control group], French versions). A laminated print of the hemodynamic protocol of the intervention group will be made available at the bedside of enrolled patients allocated to this group. Data will be entered in the electronic case report form by delegated team members and will be monitored by trained clinical research assistants designated by the sponsor. The digitalized version of the case report form is provided in Supplemental Material 6 (French version). Subjects will be assessed daily while hospitalized in the ICU.

Day 28 and day 90 assessments will be performed by investigators or delegated team members using (in ranked order): electronic medical records, phone calls to the patient’s general practitioner, phone calls to any medical doctor involved in the patient’s care after ICU discharge, and phone calls to the patients or his next-of-kin. A prescription to perform a plasma creatinine concentration measurement at day 90 will be sent by mail to ICU survivors weaned of RRT during their ICU stay, and its results communicated to the general practitioner as well as to the investigators to compute the MAKE-90 secondary outcome. Control of long-term renal function after acute kidney injury is recommended by experts [27].

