### Plans to promote participant retention and complete follow-up {18b}

Incomplete follow-up during ICU stay is not expected, given the studied population. Given that most outcomes (hemodynamic and physiologic monitoring, CRRT settings including UF_NET_, vasopressor, and mechanical ventilation and their weaning date) are specific to the ICU environment and stay of the participants, we do not expect missing values. Especially, input and output components of the primary outcome measure are reported every 4 h in the electronic ICU medical records and charts, either automatically or by the nursing staff at the bedside.

The procedure regarding the collection of the input and output components of the primary outcome and the procedure in case of missing values are detailed in SM3, Supplemental Table 3.

Missing values at day 28 or day 90 (vital status, day 90 creatinine, RRT weaning date) could occur for surviving patients after hospital discharge. Upon enrollment, patients’ and their next-of-kin contact information will be stored in the digital health record at each study site. Data regarding the vital status and RRT at day 28 or day 90 of inclusion will be retrieved following the ranked procedure described above.

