#### Analysis of the secondary outcomes

All secondary outcome measures will be analyzed in the ITT population (see section for definition). The following outcomes will be reported with median and interquartile range (with minimum and maximum values) in each study group and compared between the groups using Mann-Whitney’s test:Vasopressor-free day (secondary outcome #4)Normalized cumulative fluid balance (secondary outcome #7)Normalized cumulative UF_NET_ (secondary outcome #8)Ventilator-free day (secondary outcome #10)Hospital/ICU length of stay (secondary outcomes #12)

The secondary outcomes listed below will be reported longitudinally over time (from inclusion to H72) in the ITT population and compared between the study groups using mixed effects regression models with a fixed interaction of group by time, and a random effect with the patient identifier to account for the repetition of measurements, as well as an offset accounting for baseline values. In case of a significant interaction, a post hoc multiple comparison analysis between study groups will be performed, adjusted for the repetition of tests by the Tukey method.Number of hemodynamic instability episodes (secondary outcome #1)Number of hemodynamic instability episodes with preload dependence (secondary outcome #2)Hemodynamic parameters (secondary outcome #3)Total SOFA score and hemodynamic SOFA score (secondary outcome #5)PaO_2_/FiO_2_ ratio and extravascular lung water index (secondary outcomes #9)

The following categorical outcomes will be reported with count and percentage in each study group and compared between groups using the chi-squared or Fisher exact test: severe adverse events and adverse events of special interest, vital status (secondary outcome #6), and MAKE-90 (secondary outcome #11). Finally, no statistical test will be performed with secondary outcome #12. The hemodynamic profiles identified by the hemodynamic protocol of the intervention group will be reported in the supplemental results of the study.

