### Methods in analysis to handle protocol non-adherence and any statistical methods to handle missing data {20c}

The ITT population will consist of all enrolled patients, fulfilling eligibility criteria (inclusion and exclusion), analyzed as per their allocation group, regardless of their adherence to the protocol and the UF_NET_ rates they received, and followed until day 90 after inclusion, loss to follow-up, or death, whichever comes first. All secondary outcomes will be analyzed in the ITT population.

The modified ITT is a subset of the ITT population comprising all patients alive at 72 h of inclusion, fulfilling eligibility criteria (inclusion and exclusion), analyzed as per their allocation group, regardless of their adherence to the protocol and the UF_NET_ rates they received, and followed until day 90 after inclusion, loss to follow-up, or death, whichever comes first. This population hence will not include patients who died before H72 or those who ceased trial participation before H72. The primary outcome will be analyzed in the modified ITT population.

The rate of missing data per variable will be reported. No imputation of missing data is planned, and missing data will not be replaced.

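### The no-imputation rule drops survivors without a day-90 creatinine from MAKE-90 but keeps every known death and RRT-dependent patient, so the reported rate is probably too high

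*Protocol article*

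**What the plan says.** All references are to the protocol article.

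- **Definition** (Outcomes {12}, efficacy outcome #11): "MAKE-90 comprises death before or at day 90, RRT dependence at day 90, and persistent stage 2 or 3 acute kidney injury". The kidney-injury component compares a baseline creatinine with a day-90 value: "and the plasma creatinine measured at day 90". For the baseline value only, there is a fallback: "In case of missing baseline creatinine value, it will be retrospectively estimated".
- **Collection** ({18a}): a prescription for the day-90 test "will be sent by mail to ICU survivors weaned of RRT during their ICU stay". Day-28 and day-90 status is otherwise sought through a ranked search of records, general practitioners, other doctors, and the patient or next of kin.
- **Expected gaps** ({18b}): "Missing values at day 28 or day 90 (vital status, day 90 creatinine, RRT weaning date) could occur for surviving patients after hospital discharge".
- **Analysis** ({20a}): MAKE-90 is given as count and percentage and "compared between groups using the chi-squared or Fisher exact test".
- **Population and missing data** ({20c}): "All secondary outcomes will be analyzed in the ITT population". On missing values: "No imputation of missing data is planned, and missing data will not be replaced". The missing rate per variable will be reported.

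**The concern.** Whether MAKE-90 can be scored depends partly on its value. A patient known to have died, or known to be on RRT at day 90, is an event with no laboratory result. A survivor off RRT cannot be scored either way without the day-90 creatinine, which relies on an outpatient test arranged by mail. With no imputation or replacement, such a patient has no MAKE-90 value and leaves both the percentage and the test.

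The exclusions therefore fall most heavily on a group whose event risk is probably below that of the patients who remain. That is a bias and not only a loss of precision, and the resulting proportion is not an ITT proportion although {20c} assigns this outcome to the ITT population. The Discussion says the trial should help design a larger one with a patient-centred primary outcome, so an inflated event rate could carry into that planning.

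**Working it through.** **Plan's own figures.** The protocol gives no MAKE-90 event rate and no missing rate, so there is nothing of its own to reproduce for this outcome. Sample size {14} supplies the denominator. A 4000 ml difference with SD 4000 ml, two-sided 0.05 and 80% power gives 16 per arm, 32 in total. Dividing by 0.75 for each of the two 25% allowances gives 32/0.75 → 43 and 43/0.75 → 58, as stated. Here 58 is only an illustrative denominator.

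**Symbols.** All three values are assumptions; none is in the documents.
- D: share dead or on RRT by day 90, taken as always known; S = 1 − D. The only mortality anchor is the 25% expected by 72 h ({14}).
- q: share of S with persistent stage 2–3 kidney injury.
- m: share of S with no day-90 creatinine, missing at random within S.

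**Formulas.**
- True rate T = D + S·q
- Complete-case rate C = [D + S(1−m)q] / [D + S(1−m)]
- Difference C − T = D·S·m·(1−q) / (1 − S·m), which is positive for every D between 0 and 1, m > 0 and q < 1.

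**Example, D = 0.50, q = 0.20.** T = 0.50 + 0.50 × 0.20 = 60.0%. At m = 20%, C = (0.50 + 0.50 × 0.80 × 0.20)/(0.50 + 0.40) = 0.58/0.90 = 64.4%.

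| m | Complete-case rate | Overstatement (points) |
|---|---|---|
| 10% | 62.1% | 2.1 |
| 20% | 64.4% | 4.4 |
| 30% | 67.1% | 7.1 |

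**Range.** Over D = 0.25–0.70, q = 0.10–0.50 and m = 10–30%, the overstatement runs from about +1.0 (D = 0.25, q = 0.50, m = 10%: 62.5% becomes 63.5%) to about +7.9 (D = 0.50, q = 0.10, m = 30%: 55.0% becomes 62.9%). Patients dropped, 58·S·m, run from about 2 to 13.

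**Heavier missingness.** Assume 50% day-90 mortality, RRT dependence in 10% of survivors and persistent injury in 15% of the rest, so D = 0.55, S = 0.45, q = 0.15. The true rate of 61.8% becomes 66.4%, 69.0% and 72.0% at m = 20%, 30% and 40%. With mortality varied from 40% to 60%, m = 40% gives about +9 to +11 points.

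**When the missing include events.** If a share μ of all patients is missing and their true event risk is e, then C − T = μ(C − e). The bias is upward only while e is below the observed rate. Take 58 patients: 29 known dead or on RRT, 29 survivors off RRT, 6 of them missing, and 5 events among the 23 observed. Then C = 34/52 = 65.4%.

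| Event risk in the 6 missing | True rate |
|---|---|
| 0% (best case) | 34/58 = 58.6% |
| 20% | 35.2/58 = 60.7% |
| 50% | 37/58 = 63.8% |
| 70% | 38.2/58 = 65.9% |
| 100% (worst case) | 40/58 = 69.0% |

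The sign reverses once more than about 65% of the missing had an event.

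**Between arms, q = 0.20.**
- Equal 20% missingness with D = 0.60 v 0.45: the true difference of 12.0 points (68.0% v 56.0%) becomes 11.7.
- Identical arms (D = 0.50) with 10% v 30% missing: 62.1% v 67.1%, a spurious 5.0 points.
- For scale, with 29 per arm and a rate of 60%, the standard error of the difference is √(2 × 0.6 × 0.4/29) ≈ 13 points.

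**The case against.** **Who can be missing.** A reader might infer that only survivors off RRT can lack a MAKE-90 value. Section {18b} does not support that: it also names vital status and RRT weaning date. A patient discharged alive who later died untraced, or whose continuing RRT went unrecorded, is a missing event. This stands, and it makes the size of the bias uncertain.

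**What is dropped.** A reader might also infer that the dropped patients are mainly non-events. All participants enter with stage 3 kidney injury, persistent stage 2–3 injury is itself an event, and no rate for it is given. That inference is not supported, but upward bias needs only a risk below the observed rate.

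**Amount.** Section {18b} says only that values could be missing, and {18a} describes an active ranked search. Missingness of 20–40% has no source in the documents and may prove too high.

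**Conflict between sections.** Estimating a missing baseline creatinine in {12} might look like a contradiction of {20c}. It reads more naturally as a specific rule beside a general one; a cross-reference is enough.

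**Safeguards.** Each component will be evaluated separately and missing rates reported. This exposes the problem, and readers could build bounds from the counts, but the composite percentage and its test remain uncorrected.

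**Left to the analysis plan.** Sensitivity analyses commonly are. The no-imputation rule, however, is stated here without an exception for day-90 creatinine.

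**Multiple imputation at this size.** With D = 0.55, about 26 of 58 patients (58 × 0.45) would be survivors off RRT. With 20% missing, about 21 are observed, with some 3 events at q = 0.15. A model with several predictors would be fragile. This stands and shapes the fix.

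**Conclusion.** The point holds in limited form. Followed as written, the plan keeps all known deaths and known RRT dependence and drops discharged survivors without a day-90 creatinine. If creatinine is missing at random among survivors off RRT, MAKE-90 is overstated in each arm, by an amount that depends entirely on assumed inputs. The direction is likely but not certain, since it turns on the event risk in the missing.

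A reader might infer that the rule creates a false treatment effect. The documents do not support that. With equal missingness the contrast barely moves, and they give no reason to expect unequal return, although it is possible in an open-label trial. Any such distortion would also be smaller than the sampling error at this size. MAKE-90 is a secondary outcome, and the Discussion does not name it as the endpoint of the next trial; it mentions renal recovery and survival among possible patient-centred outcomes. The matter is worth correcting because the correction is cheap, not because it threatens the trial's main conclusion.

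**What to change.** Amend {20c}, and the analysis plan to match, as follows.

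1. Exempt MAKE-90 from the no-imputation rule and keep every ITT patient in the denominator.
2. For survivors known to be off RRT with no day-90 creatinine, pre-specify one rule: classify from the last available creatinine against baseline, or use a simple multiple imputation within that group. An imputation model with many predictors should be avoided or kept supportive.
3. Report best-case bounds (all missing are non-events) and worst-case bounds (all missing are events). Carry patients whose vital or RRT status is itself unknown through these bounds.
4. Report missingness of MAKE-90 and of each component by arm.
5. Note in {20c} the existing exception for baseline creatinine in {12}.

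The cost is wording and a small amount of analysis, with no new data. The downside is reliance on a last-value or missing-at-random assumption for a few patients; the bounds show how much the result depends on it.

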### Plans to give access to the full protocol, participant-level data, and statistical code {31c}

After the publication of the trial’s results, the full study protocol, participant-level data, and statistical code will be made available upon reasonable request. Data access request will be reviewed by the trial steering committee.

### Composition of the data monitoring committee, its role, and reporting structure {21a}

The study will be conducted in concordance with Good Clinical Practices and French regulation. The study does not declare a data and safety monitoring board as the intervention is considered as low risk and is applied in a population of patients at high risk of death, regardless of study procedures.

### Adverse event reporting and harms {22}

Due to the severity of the disease of the enrolled population, the list of reported adverse events was restricted to significant severe adverse events and adverse events of special interest. Adverse events are graded using the Common Terminology Criteria for Adverse Events (CTCAE) [29]. The list of reported severe adverse events, reported adverse events of special interest, and non-reported adverse events is given in SM3, Supplemental Table 4.

Significant severe adverse events were as follows (all with CTCAE grade ≥ 3): any kind of shock, worsening hemodynamic status, ventricular arrhythmia, myocardial infarction without ST elevation, hemorrhagic stroke, worsening respiratory status without mechanical ventilation, acute liver failure, gastro-intestinal stress ulcer, ischemic colitis, severe metabolic alkalosis, catheter-related bloodstream infection, ventilator-acquired pneumonia, documented bloodstream infection, and other documented hospital-acquired infections [29]. Significant severe adverse events will be systematically reported in the case report form in a daily manner, from inclusion to the patient’s end of participation.

Adverse events of special interest were death (CTCAE grade 5), hypovolemic non-hemorrhagic shock, successfully resuscitated cardiac arrest, myocardial infarction with ST elevation, ischemic stroke, hydrostatic acute pulmonary edema, mesenteric ischemia, acute limb ischemia, any other de novo organ ischemia, and any adverse events of grade 3 or more [29].

Given the severity of the disease of participants, some adverse events will be excessively frequent and will not be reported. Adverse events of special interest will be immediately reported to the study sponsor (Hospices Civils de Lyon), in a structured report form. Any adverse events associated with death during the study period are systematically and immediately declared and reported. Any unexpected severe adverse event will be reported to the French Regulatory Agency and the human research ethics committee.

All adverse events will be managed as per the best available standard of care. All severe adverse events will be reported in the final results of the trial.

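### The special-interest class ends with a grade ≥ 3 catch-all that absorbs all 14 listed severe events, so the two safety classes compared between arms are nested

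*Protocol article*

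**What the plan says.** The section on adverse event reporting and harms {22} explains that, because enrolled patients are so ill, "the list of reported adverse events was restricted to significant severe adverse events and adverse events of special interest". It then describes two reported classes.

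- **Severe events.** The list opens "Significant severe adverse events were as follows (all with CTCAE grade ≥ 3): any kind of shock" and has 14 entries, all under that grade condition. The route is the case report form: "Significant severe adverse events will be systematically reported in the case report form in a daily manner", until the end of participation.
- **AESIs.** Nine events are named: death, hypovolemic non-hemorrhagic shock, resuscitated cardiac arrest, ST-elevation infarction, ischemic stroke, hydrostatic pulmonary edema, mesenteric ischemia, limb ischemia, and other new organ ischemia. A general item follows, so the list closes with "any other de novo organ ischemia, and any adverse events of grade 3 or more". The route is a structured report: "Adverse events of special interest will be immediately reported to the study sponsor".

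The section adds that "some adverse events will be excessively frequent and will not be reported". It places the full lists, including the non-reported events, in Supplemental Table 4 of Supplemental Material 3, which is not shown here.

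In the analysis of the secondary outcomes {20a}, the categorical outcomes given as count and percentage per arm and compared by chi-squared or Fisher exact test include "severe adverse events and adverse events of special interest, vital status (secondary outcome #6), and MAKE-90".

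**The concern.** A special-interest class is useful when it is narrow: it picks out the harms that the intervention might plausibly cause and keeps them visible. Here those would be ischemia and hypovolemic shock under fluid removal. The grade ≥ 3 item turns the narrow class into the wider of the two.

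Three things are at stake. First, the between-arm AESI comparison may no longer describe special-interest events. Second, immediate reports of the named events reach the sponsor mixed with every other grade ≥ 3 event of intensive care. Third, a site that works from the severe-event list alone would make a daily entry, whereas a site that applies the general item would also send an immediate report. The trial is open-label with unblinded outcome assessors {17a}, so uneven use of so elastic a category could affect the comparison. It also has no data and safety monitoring board {21a}, which gives specific event reporting more weight.

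**Working it through.** The plan states no figure on this point, so there is none to reproduce. The check sets the lists side by side.

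**1. Nesting.**
- Severe class, with its entry condition "Significant severe adverse events were as follows (all with CTCAE grade ≥ 3": shock of any kind, worsening hemodynamic status, ventricular arrhythmia, infarction without ST elevation, hemorrhagic stroke, worsening respiratory status, acute liver failure, stress ulcer, ischemic colitis, metabolic alkalosis, catheter-related bloodstream infection, ventilator-acquired pneumonia, documented bloodstream infection, other hospital-acquired infection. Total 14.
- AESI class: nine named events plus every event of grade ≥ 3.
- Each of the 14 has grade ≥ 3, so 14 of 14 satisfy the general AESI item. The severe class is a strict subset of the AESI class. Counted by patient, the AESI proportion can never be below the severe-event proportion in either arm.

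**2. Overlap without the general item.** The named entries also collide.

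| Severe list | AESI list |
|---|---|
| Shock of any kind | Hypovolemic non-hemorrhagic shock |
| Ischemic colitis | Other new organ ischemia |
| Infarction without ST elevation | Other new organ ischemia |

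Deleting the general item alone would therefore not make the classes distinct.

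**3. Routes.** A listed severe event is entered daily in the case report form because it is on the severe list, and is sent at once to the sponsor because it is an AESI. Both can be done. But every severe event then has the same urgency, and the two-class structure no longer sorts events by it. The restriction of reporting to two classes becomes reporting of any grade ≥ 3 event.

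**4. Non-reported events.** These conflict with the general item only if at least one of them can reach grade 3. The article sets no grade ceiling for them and names none, so this cannot be settled from what is shown.

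**5. Effect on the comparison, if AESIs are pooled.** The planned enrollment is 58, or 58 / 2 = 29 per arm {14}. The documents give no rate of grade ≥ 3 events, so the rates below are assumptions. Two-sided Fisher exact tests:

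| Event counted | Intervention | Control | p |
|---|---|---|---|
| Named AESIs only | 8/29 (28%) | 1/29 (3%) | 0.025 |
| Any grade ≥ 3 | 29/29 | 26/29 (90%) | 0.24 |
| Any grade ≥ 3 | 29/29 | 25/29 (86%) | 0.11 |
| Any grade ≥ 3 | 29/29 | 24/29 (83%) | 0.052 |
| Any grade ≥ 3 | 29/29 | 23/29 (79%) | 0.023 |

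The last four rows are the most extreme excess possible at each control rate. Once about 80% of control patients have a grade ≥ 3 event, a pooled AESI proportion has almost no room to show harm.

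A high rate is plausible from the protocol's own description. All patients are on vasopressors with stage 3 kidney injury {10}, a quarter are expected to die by 72 hours {14}, and grade ≥ 3 worsening of hemodynamic status is itself a listed event. That is an argument for plausibility, not an estimate.

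**The case against.** **Read literally, nothing is undefined.** This is correct. Every grade ≥ 3 event goes to the sponsor at once, and the 14 listed events also go in the case report form. Recording and expedited notification are compatible. The comparison has a stated summary and test. Auditing of adverse event reporting is planned per batch of 2 to 4 participants {23}, which would limit differences between sites. That sites will diverge is a risk, not something the documents show.

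**A reader might infer that the general item contradicts the non-reported list.** The documents do not support this. The list is in Supplemental Table 4, and if it holds only grade 1 or 2 events there is no conflict. A contradiction is possible and not proven.

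**A reader might also infer that the trial cannot show an excess of ischemia or hypovolemic shock.** That is too strong. The analysis section does not say that AESIs are pooled into one proportion, and tabulation by type is compatible with its text and commonly left to the analysis plan. The section on harms also promises that all severe adverse events will be reported in the results. Hemodynamic harm has its own outcomes: instability episodes (#1), episodes with preload dependence (#2), hemodynamic variables and lactate (#3) and mortality (#6). A safety look at 72-hour mortality after 20 patients is planned {21b}. None of these depends on the AESI definition.

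**Over-inclusive notification is the cautious direction.** This also stands. Removing grade ≥ 3 events from immediate reporting would narrow notification in a trial without a safety board. It is a reason to separate the notification rule from the AESI definition, not a reason to leave the two merged.

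What the objections do not remove is the nesting. Both lists are printed in the article, and their overlap does not depend on the missing table.

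**Conclusion.** The defect is one of classification, and it is certain on the printed text. The AESI class contains all 14 severe-event categories, the named entries overlap as well, and the declared restriction of reporting has no effect for events of grade ≥ 3. The two classes compared between arms are not distinct, and an AESI proportion taken literally measures any grade ≥ 3 event instead of the nine named events, eight besides death.

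How much information is lost is conditional. It matters only if AESIs are pooled, and it becomes severe only if grade ≥ 3 events are very common. A range of 80 to 100% is an assumption that the documents neither give nor exclude. The point should be corrected. It does not threaten the primary outcome or the hemodynamic safety outcomes.

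**What to change.** 1. For classification and analysis, define AESIs as the named events only, without the general grade ≥ 3 item.
2. Assign each overlapping entry to one class. For example, count hypovolemic non-hemorrhagic shock as an AESI and limit the severe-list entry to other forms of shock. State likewise where ischemic colitis and infarction without ST elevation belong.
3. In the analysis of the secondary outcomes, compare the named AESIs, in total and by type, separately from the other grade ≥ 3 severe events.
4. If the sponsor wants every grade ≥ 3 event notified at once, write this as a separate reporting rule outside the AESI definition, and reconcile it with the non-reported list in Supplemental Table 4.

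The cost is protocol wording and a change to the event form, with no extra data. If the rule in step 4 is kept, notification is not narrowed. If it is dropped, some unlisted grade ≥ 3 events would no longer reach the sponsor immediately, and the sponsor should make that choice explicitly. The existing rules for deaths and for unexpected severe events would be unaffected.
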